## Abstract

**Background:**

Osteoarthritis (OA) is a chronic and painful condition where the articular cartilage surfaces progressively degenerate, resulting in loss of function and progressive disability. Obesity is a primary risk factor for the development and progression of knee OA, defined as the “metabolic OA” phenotype. Metabolic OA is associated with increased fat deposits that release inflammatory cytokines/adipokines, thereby resulting in systemic inflammation which can contribute to cartilage degeneration. There is currently no cure for OA. Prebiotics are a type of dietary fiber that can positively influence gut microbiota thereby reducing systemic inflammation and offering protection of joint integrity in rodents. However, no human clinical trials have tested the effects of prebiotics in adults with obesity suffering from knee OA. Therefore, the purpose of this double-blind, placebo-controlled, randomized trial is to determine if prebiotic supplementation can, through positive changes in the gut microbiota, improve knee function and physical performance in adults with obesity and knee OA.

**Methods:**

Adults (*n* = 60) with co-morbid obesity (BMI > 30 kg/m^2^) and knee OA (Kellgren-Lawrence grade II–III) will be recruited from the Alberta Hip and Knee Clinic and the Rocky Mountain Health Clinic and surrounding community of Calgary, Canada, and randomized (stratified by sex, BMI, and age) to prebiotic (oligofructose-enriched inulin; 16 g/day) or a calorie-matched placebo (maltodextrin) for 6 months. Anthropometrics, performance-based tests, knee pain, serum inflammatory markers and metabolomics, quality of life, and gut microbiota will be assessed at baseline, 3 months, 6 months (end of prebiotic supplementation), and 3 months following the end of the prebiotic supplementation.

**Clinical significance:**

There is growing pressure on health care systems for aggressive OA treatment such as total joint replacement. Less aggressive, yet effective, conservative treatment options have the potential to address the growing prevalence of co-morbid obesity and knee OA by delaying the need for joint replacement or ideally preventing its need altogether. The results of this clinical trial will provide the first evidence regarding the efficacy of prebiotic supplementation on knee joint function and pain in adults with obesity and knee OA. If successful, the results may provide a simple, safe, and easy to adhere to intervention to reduce knee joint pain and improve the quality of life of adults with co-morbid knee OA and obesity.

**Trial registration:**

Clinical Trials.gov NCT04172688. Registered on 21 November 2019.

## Background

Osteoarthritis (OA) is a chronic joint condition where the articular cartilage surfaces progressively degenerate, resulting in loss of joint range of motion, decline in function, progressive disability, pain, and reduced quality of life [1, 2]. Given its role in ambulation, knee OA is of particular concern and can lead to decreased quality of life, dependency, depression, and early death [3]. The treatment of OA is costly with an estimated $27 billion in direct and indirect costs annually in Canada [3]. A substantial portion of costs are attributed to loss of working days and the costs to cover aggressive surgical interventions such as a total knee replacement [3–5].

It is now well established that obesity is a primary risk factor for both the incidence and progression of OA [6–8]. OA linked to obesity has been defined as a separate “metabolic OA” phenotype [9, 10], representing 60% of the OA population [11]. Metabolic OA is associated with increased fat deposits that can release inflammatory cytokines/adipokines, thereby resulting in low-level systemic and local inflammation, which contributes to cartilage degeneration [12–14]. Currently, there is no cure or disease modifying treatment for OA, and the co-occurrence of knee OA and obesity accentuates the challenges associated with adherence to exercise interventions aimed at reducing body weight, improving joint function, and alleviating knee joint pain. However, obesity is considered a modifiable risk factor [8, 15] and diet interventions that target metabolic health may offer a window of opportunity to reduce systemic inflammation, thereby reducing knee joint pain and enabling participants to engage in exercise interventions to improve knee joint function.

Prebiotics are defined as a substrate that is selectively utilized by host microorganisms conferring a health benefit [16]. Inulin and/or oligofructose are two chicory root-derived prebiotics that are fermented in the gut and promote the growth of beneficial bacteria including *Bifidobacterium* [16]. The fermentation of prebiotics by intestinal bacteria results in the production of short-chain fatty acids (SCFA) which in turn can act as signaling molecules to influence host metabolism, immunity, and inflammation [17]. Part of the protection provided by SCFA is plausibly linked to their importance, particularly butyrate, in maintaining the epithelial barrier and preventing the translocation of bacterial proinflammatory molecules (e.g., lipopolysaccharide) across the gut wall [18, 19]. In clinical studies with individuals with overweight or obesity, prebiotics have been shown to reduce inflammation [20], improve glucose homeostasis [21–23], reduce body fat [24, 25], and improve appetite control [26, 27].

Rios et al. [28] and Schott et al. [29] recently showed that prebiotics can, through positive changes in gut microbiota, reduce systemic inflammation and offer protection to joint articular cartilage in rodent models of knee OA. More specifically, Rios et al. [28] showed that despite the intake of a high-fat/high-sucrose (HFS) diet, rats supplemented with the prebiotic oligofructose had significantly reduced knee joint damage, microbial dysbiosis, endotoxin levels, and insulin resistance compared to those consuming the HFS diet alone. Importantly, all of the indicated outcome measures were restored to levels observed in healthy lean chow-fed control animals [28]. Findings from this pre-clinical model suggest that obesity-related metabolic dysregulation and microbial dysbiosis play a role in the progression of metabolic OA. Modulating dysbiosis and metabolic dysfunction with prebiotic supplementation might protect against the development of knee joint damage. Similarly, Schott et al. [29] reported that obese mice fed prebiotic oligofructose were completely rescued from the joint degeneration seen in untreated obese mice and this was accompanied by reduced synovial inflammation and proinflammatory serum cytokines alongside a 1000-fold increase in the abundance of the beneficial bacterium *Bifidobacterium pseudolongum* and reduced abundance of proinflammatory bacteria *Peptostreptococcaceae* sp. and *Peptococcaceae rc*4-4 sp [29]. Despite this promising pre-clinical evidence for the protective effect of prebiotics on knee joint integrity, there are no human clinical trials in which the effects of prebiotics have been studied in adults with obesity also suffering from knee OA which represent a significant subset of idiopathic OA patients.

Prebiotics are a potentially innovative, inexpensive, and easy to adhere to intervention that could be used for the conservative management of OA patients. The aim of this study is to examine if prebiotic oligofructose-enriched inulin reduces knee joint pain and improves knee function, thereby improving quality of life through beneficial changes in gut microbiota and the reduction of systemic inflammation.

### Objectives

#### Primary objective

The primary objective of the present study is to determine if a 6-month prebiotic dietary intervention can improve knee joint function and physical performance in adults with obesity and knee osteoarthritis.

#### Secondary objectives

The secondary objectives are to determine if a 6-month prebiotic intervention can reduce knee pain, alter body composition (fat mass and lean mass), and improve quality of life. A mechanistic understanding of the potential changes will be investigated by examining changes in gut microbiota, serum inflammatory, and metabolomic markers in participants treated with the prebiotic supplement or placebo.

We hypothesize that prebiotic oligofructose-enriched inulin will reduce systemic inflammation, thereby alleviating knee joint pain and improving knee joint function. The intervention would be successful if it reduced knee joint pain sufficiently to enable participants to engage in a future exercise intervention with the goal to further increase knee joint function and reduce body fat, and thereby delaying/preventing the need for aggressive surgical intervention such as knee joint replacement.

## Methodology

### Ethics, consent, and permission

The present study has been approved (REB17-2363) by the Conjoint Health Research Ethics Board of the University of Calgary (Calgary, AB, Canada). All protocol modifications will be reviewed and approved by the ethics board. Voluntary, written, informed consent will be obtained from each participant. The trial has been registered at www.ClinicalTrial.gov (NCT04172688).

### Design, participants, and setting

The study is a single-center (all testing and visits occurring at the Human Performance Laboratory, University of Calgary, Calgary, Alberta, Canada), double blind, placebo-controlled randomized trial in which 60 adults (age 30–75 years) with obesity (body mass index (BMI) > 30 kg/m^2^) will be randomly assigned for six (6) months to either a placebo (*n* = 30; 6.6 g/day maltodextrin) or prebiotic (*n* = 30; 16 g/day oligofructose-enriched inulin) group. The prebiotic dosage selected for the present study is based on the dosage commonly used in previous studies with inulin and/or oligofructose that targeted metabolic outcomes including weight loss, adiposity, glycemia, and inflammatory markers [24–26, 30–33]. The age range was selected based on the increasing incidence rates for knee osteoarthritis that occur from the approximate age of 30 upwards [34]. We limited the upper end of the age range to 75 years given the known shift in gut microbiota composition that occurs with aging [35] that could potentially confound the study outcomes. Participants will visit the Human Performance Laboratory at baseline, 3, 6, and 9 months. At each visit, data will be collected for anthropometrics, knee function, knee pain, stool and blood samples, and questionnaires to monitor daily activities, food intake, and quality of life.

Participants will be recruited from the Alberta Hip and Knee Clinic and Rocky Mountain Health Clinic both located in Calgary, Alberta, Canada. Additionally, recruitment posters will be displayed on public notice boards and social media venues will be used to highlight the objectives of the study so that potential participants from the community in Calgary and surrounding area can contact the research team for more information. Potential participants will be screened for concomitant knee osteoarthritis and BMI > 30 kg/m^2^ and assessed for eligibility as per inclusion and exclusion criteria listed below.

### Randomization

Following confirmation from a medical doctor of a proper diagnosis of OA that fits the study criteria and alignment with the inclusion/exclusion criteria, stratified randomization of participants will occur using computer generated random numbers with an allocation ratio of 1:1 for placebo or the prebiotic intervention. The factors to be used for stratification are sex, BMI, and age. An investigator not involved in conducting the study will generate the allocation sequence and allocation (sequentially numbered) will only take place once the participant has consented to the study. The clinical trial coordinator will enroll and assign participants to the intervention groups. Participants, research staff, and those performing analysis will be blinded to the treatments and the prebiotic and placebo provided in identical opaque containers. At the end of the trial, participants will be asked to which group they believed they were assigned to assess the success of the blinding.

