### Data collection

The overall study design is depicted in Fig. 1. Participants will be assessed at the start of the diet intervention period (baseline = month 0), 3 months, 6 months (end of the diet intervention period), and 9 months (3-month wash out period following the end of the diet intervention). The primary outcome will be the change in performance-based tests in adults with obesity and knee osteoarthritis treated for 6 months with oligofructose-enriched inulin or placebo. Change in performance-based tests (30-s chair stand test, 40-m fast-paced walk test, time up & go, hand grip strength, and 6-min walk test) will be assessed by a subset of Osteoarthritis Research Society International (OARSI) tests for physical function in individuals with knee osteoarthritis. The secondary outcomes include change in knee pain, change in body composition (fat mass and lean mass), and change in quality of life in adults with obesity and knee osteoarthritis treated for 6 months with oligofructose-enriched inulin or placebo. To gain a deeper mechanistic understanding of the influence of the prebiotic on physical performance, gut microbiota composition, as well as serum inflammatory and metabolomics markers will also be assessed.

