### Analysis

Statistical analysis will be performed using SPSS 26.0 software (IBM, New York, USA). Results will be considered statistically significant if *p* ≤ 0.05. Baseline descriptive data between the prebiotic and placebo groups will be compared using chi-square for categorical variables and t tests for continuous variables. The primary analysis will be on an intent-to-treat basis, with a secondary analysis performed on a per-protocol basis with all subjects that complete the intervention. The primary outcome measurement of performance-based tests will be expressed as mean with standard deviation and analyzed using a two-way mixed model ANOVA (2 × 4) with a within-subject factor (time) of 4 levels (0, 3, 6, and 9 month time points) and one between factor (group) of 2 levels (prebiotic and placebo). A similar statistical approach will be used to test differences in the secondary outcome measurements including DXA body scans, blood tests, stool collection, and questionnaires. For the microbiota analysis, Phyloseq R package will be used for downstream analysis. Alpha diversity will be measured by calculating the Shannon and Simpson index. Beta diversity will be evaluated using non-metric multidimensional scaling (NMDS) on Bray-Curtis dissimilarity matrix. Differential abundance analysis between groups will be carried out using LEfSe conda package. To account for multiple comparisons, a false discovery rate (FDR) correction will be applied and significance set at *p* ≤ 0.05.

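### The primary 2 × 4 ANOVA uses month 0 as an outcome level and leaves out the stratification factors, which costs efficiency but not validity

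*Protocol article*

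**What the plan says.** Protocol article, Randomization: allocation uses "computer generated random numbers with an allocation ratio of 1:1 for placebo or the prebiotic intervention", and "The factors to be used for stratification are sex, BMI, and age". No cut-points for BMI or age are given.

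Protocol article, Data collection: "The primary outcome will be the change in performance-based tests in adults with obesity and knee osteoarthritis treated for 6 months". The quantity of interest is thus a change up to month 6.

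Protocol article, Analysis: the performance tests are to be "analyzed using a two-way mixed model ANOVA (2 × 4) with a within-subject factor (time) of 4 levels", and the levels are listed as "0, 3, 6, and 9 month time points) and one between factor (group) of 2 levels (prebiotic and placebo". The section names no covariate and extends a similar approach to the secondary outcomes. It also states "Baseline descriptive data between the prebiotic and placebo groups will be compared using chi-square for categorical variables", with t tests for continuous variables.

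The caption of Fig. 1 gives month 9 its own role: to show whether effects persist after the product is stopped.

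**The concern.** Two pieces of information available before treatment are not used in the comparison of the groups.

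- **Baseline value of each test.** With month 0 as a time level, the part of the model that answers the stated objective is the difference between arms in change from month 0 to month 6. A change score subtracts the whole baseline value, whatever its correlation with the later value. Regression on baseline subtracts only the part that predicts, and so is never less precise in large samples.
- **Stratification factors.** Sex, BMI and age are balanced by design but do not appear in the model. If they predict outcome, between-subject comparisons carry variance that the design has already removed.

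In addition, the 2 × 4 interaction is a 3-df test over all four visits, and the article does not single out the month-6 contrast. With 30 per arm and dropout expected, precision that can be had from data already collected is worth taking.

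**Working it through.** **The plan's own figures.** The Sample size section gives n = 21 (primary) and n = 23 (secondary) for 90% power at alpha 0.05, without an effect or SD, so neither can be recomputed. If they are per arm and two-sided, the t test implies standardized effects of about 1.03 and 0.98. The 30 per arm agrees with 23 × 1.30 = 29.9, using the 30% allowance in the Discussion.

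**Inputs.** From the article: 30 per arm, alpha 0.05, visits at 0, 3, 6 and 9 months. Assumed, because the article does not give them: baseline-to-month-6 correlation rho; equal SD at each visit, set to 1; a month-6 effect of 0.6 SD; a two-sided test.

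**Step 1: variance of the month-6 contrast.**

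- Change score: (2/n) × 2(1 − rho)
- Baseline as covariate: (2/n) × (1 − rho²)
- Ratio: (1 − rho²) / [2(1 − rho)] = (1 + rho)/2

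**Step 2: power at n = 30 per arm, effect 0.6 SD** (noncentral t, 58 and 57 df). Example at rho 0.5: the standard errors are √(2 × 1.00/30) = 0.258 and √(2 × 0.75/30) = 0.224.

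| rho | variance ratio | extra participants the change score needs (1/ratio − 1) | power, change score | power, baseline covariate |
|---|---|---|---|---|
| 0.5 | 0.75 | 33% | 63% | 75% |
| 0.7 | 0.85 | 18% | 84% | 89% |
| 0.8 | 0.90 | 11% | 95% | 97% |
| 0.9 | 0.95 | 5% | 99.9% | 99.9% |

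**Step 3: does this carry over to the planned 2 × 4 test?** The planned interaction test was simulated at 30 per arm with effects of 0.3, 0.6 and 0 SD at months 3, 6 and 9. Its power was about 62% at rho 0.5 and 84% at rho 0.7, close to the change-score column. At rho 0.8 the gain from baseline adjustment was about 0 to 2 points.

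**Step 4: the strata.** A second simulation assumed that the strata explain 20% of outcome variance with effects constant over time, under compound symmetry. The effect was half-size at month 3, full at month 6 and absent at month 9. The full effect was set separately for each rho (0.74, 0.61 and 0.45 SD), so the rows should not be compared with each other or with Step 2.

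| rho | 2 × 4 interaction | month-6 ANCOVA | ANCOVA plus strata |
|---|---|---|---|
| 0.5 | 80% | 90% | 92% |
| 0.7 | 85% | 89% | 90% |
| 0.85 | 88% | 89% | 90% |

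With the strata explaining 40% (rho 0.7), adding them raised power from 89.5% to 92.2%. The extra gain is thus about 0 to 3 points.

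Under the null, with 20% explained, the group main effect rejected in about 2% to 3% of runs instead of 5%. The group-by-time test stayed at 4.4% to 5.2%. The main effect averages in month 0, before any treatment; in the effect scenario its power was only 8% to 23%.

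**The case against.** The strongest reply is that nothing here is an error. The outcome is defined as change, the planned test addresses change, and choosing ANCOVA is a preference about method. That is right as far as validity goes: a reader might infer bias or an inflated type I error, and neither follows from the article or the calculations.

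A reader might also infer that leaving out the strata makes the main treatment test conservative. That holds only for the group main effect. Strata effects that are constant over time cancel from a change score and from the group-by-time test, which is the term that matches the stated outcome.

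The planned baseline tests could be read as a stand-in for adjustment. The article does not say so; it only says that baseline data will be compared.

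The size of the gain can also be challenged, because neither rho nor a 0.6 SD effect is in the article. If n = 21 is per arm and two-sided, the implied effect is about 1.03 SD on the change scale. At 30 per arm, power is then about 97% with the change score and 98% to 99% with the covariate, for rho from 0.9 down to 0.5. That stands.

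The reply that such detail belongs in an analysis plan does not stand. The article is not silent: it fixes a two-way model with a single between-subject factor, so a later plan that adjusts for baseline and strata would depart from the published primary analysis.

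**Conclusion.** The point holds as a loss of efficiency in the model stated in the Analysis section. Conditioning on baseline cuts the variance of the month-6 contrast by 25% at rho 0.5, 15% at 0.7 and 5% at 0.9. At the assumed 0.6 SD, that is worth about 12 points of power at rho 0.5, 5 at 0.7 and 2 or fewer from 0.8 up. Nearly all of the gain comes from baseline; the strata add little once baseline is in the model. The figures rest on the assumed correlation and effect, equal variances and, in the simulations, compound symmetry. The document does not support a claim that a fixed amount of power is being lost, or that the planned analysis is invalid. It is a worthwhile improvement, not a flaw that undermines the trial.

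**What to change.** In the Analysis section, replace the 2 × 4 ANOVA for the primary outcome with a repeated-measures model of the post-baseline values at months 3, 6 and 9. Its terms would be group, visit, group by visit, the baseline value of that test by visit, and sex, age and BMI as covariates. Name the group contrast at month 6 as primary, and keep the month-9 contrast as a secondary estimate of persistence. Use the same form for the continuous secondary outcomes. Showing baseline data descriptively, without p values, is optional.

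All the covariates are already collected. The cost is a few degrees of freedom and a protocol modification, which under the Ethics section needs ethics board approval. Recruitment began in September 2018, so the change should be filed and dated before unblinding.

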### Inclusion and exclusion criteria

Participants will be identified as eligible if they are male and female adults between 30 and 75 years of age, have a BMI > 30 kg/m^2^, and have a diagnosis of unilateral or bilateral knee osteoarthritis grades 2–3 according to the Kellgren-Lawrence radiographic rating scale. Exclusion criteria includes any previous knee joint trauma, knee surgeries, and corticosteroid injections; concomitant use of any weight loss medication or herbal weight loss products; previous bariatric or other intestinal surgery known to affect food intake or digestive function; presence of active infection, pregnancy, or lactation; regular use of a probiotic or prebiotic supplement within 3 months prior to enrollment; antibiotic use within 3 months to enrollment; weight loss > 3 kg within the preceding 3 months to enrollment; and uncontrolled cardiovascular or respiratory disease, active malignancy, or chronic infections. Eligibility will be assessed by the trial coordinator during a phone interview using a screening questionnaire.

